### Imputation procedure for missing data

We expect the occurrence of missing values due to dropout or not completely filled in questionnaires. For imputation of missing data we will use a nonparametric approach by random forest imputation respectively the R package missForest [44, 45]. The method showed better results in comparison to the Hot Deck technique, mean imputation, or multivariate imputation [46, 47]. According to MacNeil et al. [48] and Altmann et al. [49] the cost data are transformed logarithmically before imputation because they are not normally distributed and zero-inflated. After imputation, the cost data will be retransformed.

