### Outcomes

#### Primary outcome

The primary outcome is the health-related quality of life (HRQoL) particularly the mental component score measured by the SF-12 questionnaire [28, 29] six months after baseline. Patients underwent intervention are supposed to improve their psychological QoL to a greater extent than patients without intervention (comparison of means of study groups). SF-12 is the valid and tested short form of the SF-36 questionnaire [30]. It is used in many cases of cancer research (e.g. [31, 32]). HRQoL is based on self-report questionnaires filled out by the patients themselves.

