#### Intervention group

In the intervention group it has to be ensured that the baseline survey is carried out before the intervention starts. Due to the lack of time, the baseline questionnaire is issued directly by the PN. Before the patient and the PN start with the consultation the patient fills out the written baseline questionnaire (rated as consent to the survey). The consultation starts after the handing over of the baseline questionnaire to the PN. In addition to various consulting content and during the first consultation the PN unlocks the patient access to “Mein PIKKO” and offers the specialized oncological counseling. Later the PN returns the patient-filled questionnaire postage free to the evaluator.

In both groups the dates of the following questionnaires are computed dependent on the filling date of baseline, which is gathered directly after inclusion (T0). The patients are contacted to fill out questionnaires three (T1), six (T2), nine (T3) and twelve months (T4) after baseline, unless the patient withdraws the consent or dies, or changed from control to intervention group.

Baseline, main outcome and every follow-up survey consist of a set of questionnaires (see Table 1).

**Table 1 Tab1:** Directly measured patient outcomes and time of measurement

Measure	Source	T0	T1	T2	T3	T4
Demographics	Control + intervention group	X	X			
Demographics, reduced	Control + intervention group			X	X	X
Social burden	Control + intervention group	X	X			
Social support	Control + intervention group	X	X	X	X	X
Cancer, status and treatment	Control + intervention group	X	X			
Cancer, changes	Control + intervention group		X	X	X	X
Chronic diseases	Control + intervention group	X	X			
Health-related quality of life (SF-12)	Control + intervention group	X	X	X	X	X
Self-efficacy (GSES)	Control + intervention group	X	X	X	X	X
Depression (PHQ-9)	Control + intervention group	X	X	X	X	X
Anxiety (GAD-7)	Control + intervention group	X	X	X	X	X
Patient satisfaction in health care (Qualiskope-A)	Control + intervention group	X	X	X	X	X
Health literacy (HLS-EU-Q47)	Control + intervention group	X	X	X	X	X
Nutrition	Control + intervention group	X	X	X	X	X
Alcohol use and smoking	Control + intervention group	X	X	X	X	X
Intervention modules						
Use of oncological ring folder	Control + intervention group		X	X	X	X
Utilization of PN	Intervention group		X	X	X	X
Utilization of specialized oncological counseling	Intervention group		X	X	X	X

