### Sample size calculation

The three participating health insurance companies have a potential of 325,000 insured persons in the Saarland and their averaged prevalence of cancer (ICD-10-diagnosis groups C00-C97 or D45-D48) is 6.532%. Thus, the study population included (rounded up) 22,000 patients.

The financing of the PIKKO supply concept was calculated for a maximum of 1.800 patients per group, 3.600 patients in total. That means that 1.800 participants of the intervention group can benefit from the PN and the other intervention modules.

To evaluate the PIKKO intervention only 676 participants (338 per group) of the patient questionnaires are required to the statistical analyses. This number of cases was calculated with the program GPower version 3.1.7 [41]. The calculation is based on an expected effect of d = 0.25 for a two-sided t-test with same sized comparative groups, a level of significance of α = 0.05 and a power of 1-β = 0.9. The t-test refers to the primary outcome. We assumed that 338 patients would drop out and added this amount to the total number of included patients. As a consequence, the recruiting aim was *N* = 1014 = 676 + 338 patients (per group 507 = 338 reaching the end point + 169 dropout). The expected dropout rate was 33.3% regarding the baseline (338 of 1014) or respectively 50% regarding the patients reached the endpoint (338 of 676).

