### Limitations

In general, less burdened patients, patients with a stronger self-motivation, patients with higher self-efficacy or patients with more social support could preferably participate, leading to a selection bias. Related with this bias can be an overestimation of treatment effects when the treatment is especially effective for less burdened patients. Also an underestimation of the mortality or patient’s withdrawal is possible. To examine the selection bias, we included a second control group which is a random sample of eligible patients based on health insurance company data. We expect that the selection bias is small so that the generalizability of study results should be high.

The voluntary and selective participation of hospitals (respectively individual departments), clinics and practices could lead to a selective clientele of patient e.g. disproportionately many breast cancer patients. However, this could also make the study more comparable to the many studies that have been pre-determined for certain groups, e.g. specialized in breast cancer patients [18].

Due to ethical and other reasons (described in the section “Trial design”) the design is not randomized. To compensate for this limitation, we will use propensity scores for analyses [58, 59].

Since we will collect questionnaires from seriously ill and elderly patients, we might expect incomplete questionnaires. Missing items and missing complete questionnaires should be compensated by imputation of missing data [44, 45].

Each participant agrees with the use of his data from the statutory health insurance companies. These data are collected from all included patients without their direct participation. However, to collect questionnaire data, we rely on the direct support of the patients. The number of data sets can therefore vary between data from the questionnaires and from the statutory health insurance companies.

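### Six-month outcomes lost to dropout are filled once by missForest and analysed as if observed: with one third expected missing, the imputed analysis shrinks the group difference, understates its standard error, or does some of both, and no rule ranks it against the unimputed run

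*Protocol article*

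**What the plan says.** The primary outcome is health-related quality of life, "particularly the mental component score measured by the SF-12 questionnaire [28, 29] six months after baseline" (Primary outcome).

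The sample size section says: "The expected dropout rate was 33.3% regarding the baseline (338 of 1014". That is 169 of 507 patients per group, leaving 338 per group for the primary test.

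The section on imputation expects gaps both from dropout and from partly completed questionnaires, and says: "For imputation of missing data we will use a nonparametric approach by random forest imputation respectively the R package missForest". It adds that this method did better than hot deck, mean and multivariate imputation. The Limitations section confirms the scope: "Missing items and missing complete questionnaires should be compensated by imputation of missing data". No repeated draws, pooling rule or variance correction is given, and the text does not say whether study group enters the imputation.

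The Statistical methods section compares group averages by t-tests, takes regression-adjusted means from growth curve models, and runs the analyses once on imputed and once on unimputed data as a validation. It does not say which run is primary or what follows if they disagree.

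For costs, "the cost data are transformed logarithmically before imputation because they are not normally distributed and zero-inflated"; the values are transformed back afterwards.

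**The concern.** missForest returns one completed data set in which each missing numeric value is a forest prediction, in effect an estimated conditional mean. This is a property of the named method, and the article states nothing that would alter it. Two things go wrong when such values are treated as observations:

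- **Attenuation.** If group carries little weight in the forest, for example as one predictor among many, the imputed scores in both groups are pulled towards a common mean. The group difference shrinks.
- **False precision.** If group is used fully, the estimate is unbiased. However, the predicted values lack residual scatter and are counted as independent patients, so the standard error is too small.

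The two are not alternatives. A forest that includes group typically does some of each. With a third of the scores affected, either can change the conclusion on the primary outcome, and the plan leaves open whether the conclusion rests on this run.

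**Working it through.** **1. The plan's own figure.** The inputs are "an expected effect of d = 0.25 for a two-sided t-test with same sized comparative groups", with "a level of significance of α = 0.05 and a power of 1-β = 0.9". With 338 per group the noncentrality is 0.25 × √(338/2) = 3.25 and the exact t-test power is 0.9007; with 337 it is 0.8998. So 338 is reproduced. Allowing for one third dropout, 338 / (2/3) = 507 per group, 1014 in total. The sample size is correct and rests on completers, not on imputed values.

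**2. Assumptions that are not in the article.** Scores are missing at random (the simulations use completely at random). Within-group outcome variance is 1. The imputation model explains a share R² of it, shown over 0.25 to 0.6.

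**3. Group fully used in the imputation.** The estimate stays at 0.25.

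- True variance of a group mean: (1 − R²)/338 + R²/507.
- Variance the t-test reports: (2/3 + R²/3)/507.
- The standard error (SE) of the difference is √2 times the root of each.
- True type I error: 2Φ(−1.96 × reported SE / true SE).

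| R² | True SE | Reported SE | Ratio | Type I error |
|---|---|---|---|---|
| 0.25 | 0.0736 | 0.0544 | 0.74 | 15% |
| 0.40 | 0.0716 | 0.0562 | 0.78 | 12% |
| 0.60 | 0.0688 | 0.0585 | 0.85 | 10% |

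For example, at R² = 0.25 the true variance is 0.75/338 + 0.25/507 = 0.002712, the reported variance is 0.75/507 = 0.001479, and √(0.001479/0.002712) = 0.74. A simulation of linear imputation at R² = 0.25 (correlation 0.5 with baseline, 3,000 replicates) gave type I error 14.2%, in line with the formula.

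**4. No group information in the imputation.** The imputed third contributes a difference of zero: (2/3) × 0.25 + (1/3) × 0 = 0.167, an attenuation of 33%. Type I error stays near 5% (4.4% to 5.1% in simulation).

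**5. Random forest with group as one predictor.** Two simulations at 507 per group with d = 0.25 used a generic random forest, not the R package itself:

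- Group as 1 of 10 predictors, R² = 0.4, 100 trees, 110 replicates: mean estimate 0.183, attenuation (0.25 − 0.183)/0.25 = 27%.
- Group, one baseline score (correlation 0.5) and 7 noise variables, 40 trees, 300 replicates: mean estimate 0.208, attenuation 17%. The reported SE was 0.054 against an empirical 0.061 (no effect) to 0.073 (d = 0.25). Type I error was about 9%, with Monte Carlo error of about 1.7 points.

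The second simulation shows both defects at once.

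**6. Costs (secondary).** For a lognormal cost, transforming a predicted log mean back returns exp(−s²/2) of the mean, where s is the residual log SD. This is 0.61 at s = 1.0 and 0.32 at s = 1.5, for imputed values only. If 5% of costs were missing (an assumption), the overall mean would be low by 0.05 × 0.39 = 2.0% to 0.05 × 0.68 = 3.4%; at 1% missing, by less than 1%.

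**The case against.** Much of a sound analysis is already planned. The analyses are also run without imputation, growth curve models are named for the adjusted means, and the power calculation uses completers only. A growth curve model fitted by likelihood to the observed data would not have this defect. The size of the effect also depends on the predictor set. If the three-month score is observed for everyone and already carries a group difference of 0.25, it brings group information into the imputation even when group is omitted. With a common correlation of 0.5 to 0.7 between waves, the three-month coefficient is ρ/(1 + ρ) = 0.33 to 0.41, so the estimate is (2 × 0.25 + 0.33 × 0.25)/3 = 0.194 to (2 × 0.25 + 0.41 × 0.25)/3 = 0.201, rather than 0.167. This is a favourable case, since some patients leave before three months.

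All of that stands and limits the point. It does not remove it: the imputed run remains a stated analysis with wrong inference, and its standing relative to the other run is open.

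A reader might infer four stronger things that the article does not support:

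- **That the primary result is wrong outright.** Only one of two unranked analyses is affected.
- **That comparing the two runs can validate nothing.** The unimputed run is free of this artefact, so a gap between them would be informative. What fails is narrower: agreement does not vouch for the imputed standard error, and disagreement has no rule.
- **That scores are imputed after death or a change of group.** The article says only that patients are contacted for follow-up "unless the patient withdraws the consent or dies, or changed from control to intervention group". Imputing beyond those events would be an inference from silence, and the full plan may deal with it.
- **That mean costs will be far too low.** Limitations says insurer data are obtained for all included patients without their taking part, and no missing-cost rate is given. How zeros are logged is a detail an article may leave out.

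**Conclusion.** The point holds for the imputed analysis. A stated rule, single imputation by missForest of outcomes lost to dropout followed by ordinary tests, gives a shrunken group difference, an understated standard error, or some of both.

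With one third of six-month scores missing at random and d = 0.25, the forest simulations put the estimate at about 0.18 to 0.21, and at 0.167 if no group information is used. If group is fully used, the standard error ratio is about 0.74 to 0.85 and type I error about 10% to 15% over R² of 0.25 to 0.6. The sizes depend on the assumed R², predictor set and missingness mechanism. The kind of error does not.

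The unimputed run partly mitigates this, but it does not correct the imputed result, and the article does not say which of the two decides. The cost issue is secondary and cannot be sized from the article.

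**What to change.** 1. Name one primary analysis: the already planned growth curve model, fitted by likelihood to all observed mental component scores from baseline to twelve months, without imputing outcomes and with the six-month group contrast as the test. It is valid under missingness at random if correctly specified.
2. Where imputation is used, replace missForest by multiple imputation with random draws, run separately by group or with group in the model, and pooled by Rubin's rules. Label it a sensitivity analysis and state what follows if it differs from the primary result.
3. If any costs are missing, impute them on the euro scale, for example by predictive mean matching or a two-part model, and report how many were imputed.

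The cost is plan wording and some computing time. Intervals will be wider than those the imputed run would print with group fully used, by a factor of about 1/0.85 = 1.18 to 1/0.74 = 1.35. In the setting of step 3 of the working, the honest standard error of 0.069 to 0.074 is still no larger than that of the completers-only t-test, √(2/338) = 0.077. The sample size is unchanged, since 338 completers per group already give 90% power.

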### Monitoring

The numbers of enrolled patients and other organizational data are monitored and sent weekly to the consortium leader (IKK Südwest). The study progress is reported quarterly according to an approved milestone plan. All events, progress data, milestones and failures are reported annually to the sponsor. The PN are supervised quarterly by the Cancer Society of the Saarland.

### Adverse events

PIKKO is a supportive care element without invasive impact on the patients.

## Discussion

So far, there is no other project in Germany that offers cancer patients such a wide range of possibilities as PIKKO. There is also no known international study that combines PN, technical applications and course offerings. There are many technical applications, from websites [50] to apps [51, 52]. Patient navigators are also being tested [53, 54]. There are also numerous cancer advice centers [55, 56] and courses for cancer patients [57]. To bundle all these services and offer them together is an innovation of this study. Finally, the strengths and limitations of such an extensive project should be noted.

### Strengths

This new supportive care concept is intended to establish an offer for all cancer patients. Low barriers for the procurement of information such as the website, which offers both specific and general information, are just as much a part of the concept as the broad further training of PN, who can thus advise all cancer patients.

The study is designed to evaluate the effect of PIKKO interventions under naturalistic conditions. The according heterogeneity of the sample (age range, all cancer types, all sexes) tries to reflect the reality of oncological care. Due to the heterogeneity of the sample, subgroup analyses are planned to show which module of PIKKO works best for whom.

Furthermore, the longitudinal design with five measurement points allows the investigation of long-term effects.

Last, the telephone interviews with participating PN and physicians can show experiences in the implementation that help to make PIKKO a common part of cancer care.

### Limitations

In general, less burdened patients, patients with a stronger self-motivation, patients with higher self-efficacy or patients with more social support could preferably participate, leading to a selection bias. Related with this bias can be an overestimation of treatment effects when the treatment is especially effective for less burdened patients. Also an underestimation of the mortality or patient’s withdrawal is possible. To examine the selection bias, we included a second control group which is a random sample of eligible patients based on health insurance company data. We expect that the selection bias is small so that the generalizability of study results should be high.

The voluntary and selective participation of hospitals (respectively individual departments), clinics and practices could lead to a selective clientele of patient e.g. disproportionately many breast cancer patients. However, this could also make the study more comparable to the many studies that have been pre-determined for certain groups, e.g. specialized in breast cancer patients [18].

Due to ethical and other reasons (described in the section “Trial design”) the design is not randomized. To compensate for this limitation, we will use propensity scores for analyses [58, 59].

Since we will collect questionnaires from seriously ill and elderly patients, we might expect incomplete questionnaires. Missing items and missing complete questionnaires should be compensated by imputation of missing data [44, 45].

Each participant agrees with the use of his data from the statutory health insurance companies. These data are collected from all included patients without their direct participation. However, to collect questionnaire data, we rely on the direct support of the patients. The number of data sets can therefore vary between data from the questionnaires and from the statutory health insurance companies.

### Trial status

The study protocol was approved by the ethics committee of medical association of the Saarland at 2nd November 2017. The first patient of the control group was included on 23th November 2017. The control group was recruited till 31st October 2018. Since then till 31st March 2020 the intervention group was recruited. An extension of the recruitment period of the intervention group (from one year to one and a half year) was necessary due to the entry of a further statutory health insurance (AOK Rheinland-Pfalz/Saarland) in the summer of 2019.

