### Trial design

The design of the evaluation study consists of four components: patient surveys, data provided by statutory health insurance companies, interviews with service providers as well as the usage data of the oncological knowledge database. The non-randomized, controlled, comparative, multicenter, longitudinal design included three groups: experimental group (treatment as usual plus PIKKO), first control group (treatment as usual; active recruited; questionnaire and health care data) and second control group (treatment as usual; random selection, only anonymous health care data). A non-randomized design with two recruitment periods, starting with the (first) control group, was chosen due to the following reasons: 1) randomization on a test person level was not possible for ethical reasons and for reasons of the statutory basis of the German health care system. 2) It is also not reasonable from a CRM (Customer Relationship Management) perspective to withhold an existing service from needy persons on the part of the statutory health insurances. 3) In a medical facility (practice, clinic), intervention and control cannot take place simultaneously to the extent required by this study (control patients could still contact PN). 4) Cluster randomization was not feasible for a project of this size and kind due to the medical infrastructure in the small state of Saarland. Accordingly, the periods were set one after the other and later the participants of the control group have the option to switch to the intervention group. Secondly, to establish the new intervention with all the descripted modules the German Cancer Society, the Cancer Society of the Saarland and the health care insurance companies needed time, nearly one year. However, no time should be lost in terms of data collection, so it was used for the patient survey of the control group. The date of recruitment determines the group assignment. The control group is included in the first project year (while the new intervention is under development) and the intervention group is recruited in the second year (when the new consulting and information path is available). A third group is a random selected sample of patients who are not part of the two other groups. Only health care data are collected for these persons. This second control group allows examining the representativeness of the sample respectively the selection process and the comparisons of treatment courses.

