### Participant timeline

The enrollments of the two allocation groups take place in two consecutive enrollment periods. Every period lasts one year starting with the control group.

The patients express interest to participate in the supply concept to the enrollment person who reviews the inclusion and exclusion criteria. Furthermore, the enrollment person informs and educates the patient and hands over the oncological ring folder. After successful enrollment a standardized form is sent to the statutory health insurance company and to the evaluator. This informs the evaluator about the patient assignment and the agreement to establish contact (e.g. by telephone).

From this point in timeline there are small differences between the two groups in collecting the baseline data.

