### Statistical methods

Characteristics of control and intervention groups (e.g. age, sex, education, family situation, partner situation) will be analyzed with descriptive statistics. Since no randomization is made for ethical and research practical reasons, univariate tests are used to determine which of the above mentioned characteristics differ between the two groups. Ideally there are no significant differences between the two groups. In the case of significant differences we will compute propensity scores using the corresponding pre-treatment variables. Then, we will apply in the subsequent analyses propensity scores as stabilized regression weights to reduce bias caused by different group characteristics.

The main hypothesis of an intervention effect on psychological and physical health, self-efficacy, health care costs etc. will be proofed by the comparison of averages of intervention and control group (resp. t-tests). To estimate the corresponding regression adjusted group means we will use growth curve models. Furthermore, we will conduct subgroup analyses to identify conditional treatment effects.

For dropout analysis we will conduct a logistic regression with dropout as criterion and group assignment and baseline variables as predictors applying the regression weight mentioned above. For the time-to-event analysis we will conduct a Cox regression.

The level of significance will be α = 0.05. To validate our analyses, we will conduct the analyses with imputed missing data and without imputation.

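### Recruitment date alone sets the group, and the stated comparison of averages has no term for calendar time: date the planned second control group to both periods for costs, and adjust the six-month mental score for month

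*Protocol article*

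**What the plan says.** Trial design fixes the assignment: "The date of recruitment determines the group assignment". Participant timeline plans two consecutive recruitment periods: "Every period lasts one year starting with the control group". Trial status reports what happened: "The first patient of the control group was included on 23th November 2017", "The control group was recruited till 31st October 2018" and "Since then till 31st March 2020 the intervention group was recruited". It adds that "An extension of the recruitment period of the intervention group (from one year to one and a half year) was necessary", because a further insurer joined.

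Statistical methods states that the hypothesis of an effect on health, self-efficacy and costs "will be proofed by the comparison of averages of intervention and control group (resp. t-tests". Growth curve models supply adjusted means. Propensity weights are built from those patient characteristics that differ between the groups (age, sex, education, family and partner situation are the examples given). No season or calendar term is named.

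A second, randomly drawn control group has insurer data only. Trial design describes its use: "This second control group allows examining the representativeness of the sample respectively the selection process and the comparisons of treatment courses". Limitations uses it to examine selection bias. Additional data lists it as one of three groups whose insurer data serve the cost evaluation. No calendar-time role is stated for it. Limitations names selection and the lack of randomization, but not period effects.

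**The concern.** When the enrolment date decides the group and the two periods do not overlap, anything that changes with time enters the difference between the groups. For costs this means prices, tariffs and practice; for the mental component score it includes season. The stated analysis compares the two averages and relies on propensity weights to make up for the missing randomization. Weights built from patient characteristics leave a time trend where it is.

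At stake is how the cost result is read. The Objectives section expects lower costs under PIKKO. A general rise in costs between the two periods would hide a real saving, and a fall would imitate one. For the primary outcome the extension gives the intervention group a second November-to-March enrolment season that the controls do not have.

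**Working it through.** **Inputs.** Recruitment dates from Trial status; one-year periods from Participant timeline; the six-month primary endpoint from Primary outcome; d = 0.25, two-sided α = 0.05, power 0.90 and one-third dropout from Sample size calculation. Intervention recruitment is taken to start on 1 November 2018, and its planned year to end on 31 October 2019. Monthly enrolment is not given, so even accrual is assumed throughout.

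**1. The plan's own figures.** A two-sided t-test with d = 0.25 needs 337.2 per group, rounded up to 338 (power 0.9007). 338 / (1 − 1/3) = 507 per group, 1014 in total. These reproduce and are not in dispute.

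**2. Recruitment windows.** Control: 343 days, or 343 / 30.4375 = 11.3 months. Intervention: 517 days, or 17.0 months. Planned intervention year: 365 days.

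**3. Six-month (T2) windows.** Control: 23 May 2018 to 30 April 2019. Intervention: 1 May 2019 to 30 September 2020. They do not overlap.

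**4. Costs.** Under even accrual the mean enrolment date is the middle of the window.

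| | Midpoint | Days after control midpoint | Years |
|---|---|---|---|
| Control | 13 May 2018 | – | – |
| Intervention, as run | 17 July 2019 | 430 | 430 / 365.25 = 1.177 |
| Intervention, planned year | 2 May 2019 | 354 | 354 / 365.25 = 0.969 |

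Assume yearly cost growth of 3% to 5% (the documents give no rate):
- as run: 1.03^1.177 − 1 = 3.5%; 1.05^1.177 − 1 = 5.9%
- planned year: 1.03^0.969 − 1 = 2.9%; 1.05^0.969 − 1 = 4.8%

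The sequential design accounts for 354 of the 430 days; the extension adds 76.

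**5. Why weights do not help.** Given the enrolment date, the probability of being in the intervention group is 0 or 1. A propensity score with date in it has no overlap, and one without date cannot balance it.

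**6. What a dated second control group adds.** Let S be the lasting cost difference between participants and non-participants, τ the background change between periods, and P the PIKKO effect. Intervention minus contemporaneous second controls = S + P. First controls minus contemporaneous second controls = S. The difference is P; both τ and S drop out. The direct comparison of averages gives P + τ. The result needs parallel trends: τ must be the same in participants and non-participants, and S the same in both periods.

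**7. Season at T2.** T2 falls in May to September when enrolment falls in November to March.
- Control: 129 of 343 days = 37.6%
- Intervention as run: (151 + 152) of 517 = 303 / 517 = 58.6%
- Intervention, planned year: 151 / 365 = 41.4%

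Bias under two assumed seasonal patterns:
- A step of 0.1 to 0.3 SD between these months and the rest: (0.586 − 0.376) × 0.1 to 0.3 = 0.021 to 0.063 SD. In the planned year it is (0.414 − 0.376) × 0.1 to 0.3 = 0.004 to 0.011 SD.
- A yearly sinusoid of amplitude A: at most 0.25A. With A = 0.05 to 0.20 SD this is 0.013 to 0.05 SD.

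The step split uses exactly the months that the extension duplicates, so it leans towards a large contrast. For change from baseline the sinusoid limit is about 0.5A (0.025 to 0.10 SD), because baseline season is unbalanced in the opposite direction.

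**8. Restricting to the planned year.** If 507 intervention patients were enrolled evenly and one third dropped out, 338 × 365 / 517 = 239 would remain. Against 338 controls, power at d = 0.25 falls from 0.90 to 0.84.

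**The case against.** Sequential recruitment is a disclosed choice. Trial design gives four reasons against randomization and cites the set-up time of nearly a year. A condensed article may leave the second control group's observation window and the cost model to the full plan. Both points are fair. The criticism is therefore not that details are missing, but that the comparison the article does state cannot separate trend from effect, and that its list of limitations omits this.

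Calendar time is not wholly tied to group in the data. Control follow-up questionnaires run to about October 2019, while intervention baselines, taken before the intervention starts, begin about November 2018. The growth curve models use these repeated measures. Control cost follow-up also reaches into the intervention period, to about April 2019 at the data cut in Table 2. This allows some separation, and is why the claim below says not fully separable. It does not give calendar time a place in the stated comparison.

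Four stronger readings are tempting but not supported:
- *The second control group is left out of the cost evaluation.* Additional data includes it. What is absent is a calendar-time role.
- *The extension causes the confounding.* For costs, 354 of 430 days were already planned. The extension mainly affects season.
- *Season could produce the expected effect.* With a sinusoid, d = 0.25 at six months would need A of about 0.25 / 0.25 = 1 SD.
- *The second control group could also correct the primary outcome.* It has no SF-12 data.

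**Conclusion.** The concern holds as a cheap improvement to the stated method. Group and recruitment period coincide, and the planned comparison of averages with patient-characteristic weights leaves any calendar trend in the group difference.

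For costs the size is 3.5-5.9% at an assumed growth of 3-5% a year and even accrual, and most of it comes from the planned design. If costs rise, the bias works against PIKKO.

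For the six-month mental score the seasonal imbalance is clear under even accrual, but the bias is probably small: about 0.01-0.06 SD under assumed swings, against a design effect of 0.25 SD. Its direction cannot be told from the documents.

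The figures do not support making the planned 12-month intervention set the main analysis. That would drop 152 of 517 enrolment days and could cost 6 percentage points of power, for a problem that a covariate handles.

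**What to change.** 1. **Costs and days of inability to work.** Draw the second control group with index dates in both recruitment periods. Estimate (intervention minus contemporaneous second controls) minus (first controls minus contemporaneous second controls). State the parallel-trends assumption and the scale on which it is meant to hold. Check that the make-up of the second controls is stable across the periods, by insurer too, because a further insurer joined only during intervention recruitment.

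2. **Mental component score at T2.** Keep all intervention patients and add the calendar month (season) of T2 as a covariate. Both groups' T2 windows reach every calendar month, so season can be estimated if its pattern is taken as the same in both periods. If change from baseline is modelled, add the month of T0 as well. Show the planned 12-month intervention set as a sensitivity analysis only.

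3. **Limitations.** State that non-seasonal calendar effects on the mental score cannot be fully separated from PIKKO, since the second control group has no SF-12 data.

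The cost is analysis wording, a dated draw of a sample already planned, and one added limitation. The downside is a wider interval for the cost estimate. With equal variances, n patients per study group and m second controls per period, the standard error grows by √(1 + n/m): 1.41-fold if m = n, 1.12-fold if m = 4n. The article does not give m, so these ratios are illustrations.
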